## Abstract

**Introduction:**

The Comprehensive High-dose Aphasia Treatment (CHAT) programme is an intensive comprehensive aphasia programme, which aims to address evidence-practice gaps in aphasia rehabilitation where there are known barriers to service delivery requiring implementation strategies. The aims of this study are to (1) evaluate the clinical implementation of the CHAT programme, (2) assess the clinical effectiveness of CHAT compared with usual care in rehabilitation services and (3) determine whether the real-world implementation of CHAT compared with usual care is cost-effective.

**Methods and analysis:**

Four participant groups will be recruited across six hospital and health services Australia-wide to participate in a type 3 hybrid effectiveness-implementation study: (1) people with aphasia, (2) support persons, (3) treating clinicians and students and (4) clinical stakeholders (eg, managers). This before-and-after study will include three time periods: (1) ‘usual care’ where people with aphasia will receive their usual care aphasia therapy, (2) ‘implementation transition’ where clinicians will be trained to deliver CHAT and (3) ‘intervention implementation’ where people with aphasia will receive the CHAT programme (ie, 50 hours of evidence-based aphasia therapy over 8 weeks). Evidence-based implementation strategies will be used to facilitate implementation within participating rehabilitation services. The primary outcome is delivery of evidence-based aphasia treatment (ie, CHAT) as measured by a composite score of quality indicators. Clinical effectiveness outcomes, measuring change in language impairment, communication effectiveness, confidence and quality of life, and implementation outcomes will also be examined. We will also conduct an embedded mixed-methods process evaluation and economic evaluation.

**Ethics and dissemination:**

This study has been approved by the Royal Brisbane and Women’s Hospital Human Research Ethics Committee (HREC/2021/QRBW/72154). Outputs will include conference presentations, publications and a training package to optimise implementation of aphasia treatment in rehabilitation service contexts.

**Registration details:**

Australian New Zealand Clinical Trials Registry (ANZCTR) prospective registration ACTRN12621001765819. Trial registered 23 December 2021. https://anzctr.org.au/Trial/Registration/TrialReview.aspx?id=381365&isReview=true.

STRENGTHS AND LIMITATIONS OF THIS STUDYA hybrid implementation-effectiveness study design will support a rapid research translation and uptake of the Comprehensive High-dose Aphasia Treatment (CHAT) programme at trial completion by identifying effective implementation strategies that can be tailored to local barriers, and provide concurrent answers about intervention effectiveness in real-world settings.This study will be conducted across six Australian hospitals and health services, to compare the effectiveness and cost-effectiveness of usual care with the CHAT programme, which has been developed to address known aphasia rehabilitation evidence-practice gaps.A diversity of health services will be involved in this study (ie, metropolitan, regional, hospital-based and community-based services), which will allow us to examine implementation in different settings.This study only includes people with post-stroke aphasia who speak English, therefore limiting generalisability to other aetiologies and patients from other linguistic backgrounds.Due to the non-randomised, pre-post design with the allocation of people with aphasia based on time periods, various risks of bias are possible, including selection bias.

## Introduction

 Aphasia is a language and communication disability that affects approximately 30% of stroke patients,^1 2^ and negatively impacts quality of life more than cancer and Alzheimer’s disease.^3^ Aphasia can have devastating impacts on psychological, social and vocational aspects of life. People with post-stroke aphasia are twice as likely to have depression compared with stroke survivors without aphasia,^4^,^6^ and the presence of aphasia is associated with differences in care quality.^2^ There is high-quality evidence that aphasia therapy improves communication outcomes.^7^,^9^ Furthermore, high-level evidence supports comprehensive, tailored, high-dose aphasia therapy.^9 10^ However, this research is not often translated to clinical practice, leading to evidence-practice gaps.^11^ There are key gaps in therapy timing, intensity, goal setting and communication partner training.^11^,^14^ Addressing these gaps is important for improving aphasia care and patient outcomes.

A solution is the introduction of Intensive Comprehensive Aphasia Programs (ICAPs), including its modified versions.^15^,^19^ ICAPs have been defined as comprising a minimum of 3 hours of daily treatment over a period of at least 2 weeks and have a set start and end date, with a cohort of participants starting and finishing the programme together. ICAPs include individual and group therapy, targeting both impairment and activity/participation levels of language and communication, and include education for patients and/or families.^20^ Modified ICAPs (mICAPs) meet each of these programme elements apart from one element.^21^ There is evidence that ICAPs and their modified versions, such as the Comprehensive High-dose Aphasia Treatment (CHAT) programme,^22^ are effective and can significantly reduce aphasia severity and language impairment, and improve functional communication, psychosocial well-being and quality of life.^1922^,^26^ To increase access to quality aphasia services and to improve the health and quality of life of people living with post-stroke aphasia, the next stage of the research process is to implement mICAPs/ICAPs into clinical rehabilitation services and to evaluate clinical effectiveness, implementation strategy effectiveness and cost-effectiveness.

Successful translation of research into clinical practice takes considerable time and effort^27^ and is more likely if the implementation strategy is tailored to knowledge of barriers and enablers to change.^28^ Trebilcock *et al*^29^ identified barriers to global implementation of intensive aphasia services, with Shrubsole *et al*^30^ more recently investigating barriers to a previous iteration of CHAT (ie, the Aphasia Language, Impairment and Functional Therapy (Aphasia LIFT) programme), highlighting issues like service inflexibility and feasibility concerns within current healthcare constraints. These barriers shaped a tailored implementation strategy for the CHAT programme, incorporating evidence-based behaviour change techniques.^31 32^ The resultant implementation strategy incorporates six components including (1) executive, leadership and stakeholder support; (2) dedicated allocation of clinical staff; (3) interactive education and training programme; (4) resource procurement and provision; (5) ongoing implementation support and (6) consumer engagement and promotion, and is described in more detail elsewhere.^30^ More recently, Monnelly *et al*^33^ also explored the views of 227 speech pathologists regarding intensive and comprehensive aphasia therapy. Barriers raised included a lack of resources for ICAP delivery and a low level of optimism that ICAP delivery issues (eg, insufficient staffing, lack of funder/commissioner support) could be resolved, with only 16.5% of clinicians feeling that their service could be redesigned to implement and deliver an ICAP. This highlights the need for further implementation efforts to enable successful translation of research/clinical recommendations into clinical practice.

The aims of this study are to (1) evaluate the clinical implementation of the CHAT programme, (2) assess the clinical effectiveness of CHAT compared with usual care in rehabilitation services and (3) determine whether the real-world implementation of CHAT compared with usual care is cost-effective. We hypothesise that compared with providing usual care, implementing the CHAT programme using an evidence-based tailored implementation strategy will result in increased quality of care at a service level, as quantified using a composite outcome measure.

## Methods and analysis

### Design and setting

We will undertake a multicentre, pragmatic, prospective, non-randomised before-and-after study with three study periods (usual care, intervention transition, intervention) and an embedded mixed-methods process evaluation and economic evaluation. A type 3 hybrid implementation-effectiveness design will be employed.^34^ A before-and-after study design was selected over a randomised controlled trial due to requirements of the funding model, and to enable the equitable contribution and participation of partner sites. This study will take place across six hospital and health services, across three Australian states. Sites from a wide range of health service settings will take part in this study (ie, metropolitan, regional, in-patient and out-patient hospital-based and community-based services). The diversity of health services involved in this study will allow us to examine implementation in different settings and to enable us to develop a strong plan for future expansion to more organisations that may seek to implement the CHAT programme within Australia.

### Study periods

This study will include three time periods (see figure 1): (1) **usual care** (years 1 and 2); (2) **implementation transition** (between years 2 and 3) to allow clinicians to upskill in the implementation and delivery of the CHAT programme; and (3) an **intervention** period (years 3 and 4) for the implementation of the CHAT programme.

**Figure 1 F1:**
[figure not shown]
Pragmatic, prospective, non-randomised, before-and-after study design. CHAT, Comprehensive High-dose Aphasia Treatment.

#### Period 1: usual care

This first period of the study will examine current speech pathology clinical practices in post-stroke aphasia rehabilitation as prescribed by treating speech pathologists in accordance with health service and site procedures. Patients recruited during the usual care phase will receive standard speech pathology care, as typically provided by the health service. During this usual care period, it will be important for rehabilitation services to avoid, where possible, significant changes to their model of care and service delivery that relate to the CHAT programme. Services will be informed of this requirement and invited to discuss with the research team potential changes that could affect the study. Unavoidable changes will be recorded and monitored by the research team.

#### Period 2: intervention transition

The second period of the study will involve the transition in preparation for the implementation of the CHAT programme. This period will include stakeholders, clinicians and students in the same clinical settings which participated in period 1. During the intervention transition, meetings will be conducted with stakeholders and clinicians at each site to identify potential barriers and facilitators to CHAT implementation, identify site champions and tailor the site implementation strategy, as required. Clinicians and students will be upskilled and trained in accordance with the implementation strategy to deliver the CHAT programme to eligible patients with post-stroke aphasia.

#### Period 3: intervention

##### Comprehensive High-dose Aphasia Treatment programme intervention

Patients recruited during the intervention phase will receive the CHAT programme. The CHAT programme (previously known as the Aphasia LIFT programme in its initial iterations) was first developed and trialled by Rodriguez *et al*,^35^ and most recently, has been successfully implemented in a single metropolitan health service.^22 26^ The programme aims to address known aphasia rehabilitation evidence-practice gaps. This comprehensive aphasia treatment package uses two complementary but often isolated approaches, that is, treatment of the language impairment and its consequences on everyday communication.^35^ The CHAT programme is a modified ICAP, meeting all but the criteria for treatment intensity with respect to the defining ICAP elements. CHAT comprises 50 hours of therapy delivered in a distributed schedule over 8 weeks (see table 1). The programme includes evidence-based and goal-directed individual impairment, activity and participation, and computer-based therapy, and group sessions for education and information sharing, conversational training and discussion of topics related to living with aphasia. The CHAT programme is delivered in cohorts, whereby patients start and complete the programme at the same time. As part of this study, intervention will be delivered in-person with the option of delivery via telerehabilitation to increase access to therapy for regional patients and those discharged from hospital.

**Table 1 T1:** Core components of the CHAT programme

Programme component	No. of sessions
Goal setting session	1 (1–2 hours)
Impairment therapy (*eg, Semantic Feature Analysis, Constraint-Induced Aphasia Therapy*)	14 × 1-hour sessions
Activity and participation therapy—improving communication in context (*eg, Aphasia scripts, role-play, conversational coaching, use of compensatory strategies, conversation partner training*)	14 × 1-hour sessions
Computer therapy (*eg, Aphasia Scripts, StepByStep programme, Constant Therapy*)	14 × 1-hour sessions
Group therapy (*eg, educational sessions on stroke and aphasia, mood and well-being, psychosocial support, living successfully with aphasia*)	8 × 1-hour sessions
Independent practice (home, hospital and community rehabilitation)	–

CHAT, Comprehensive High-dose Aphasia Treatment.

Prior to commencement, individual goal setting in collaboration with the patient will be used to develop an evidence-based plan for treatment across each therapy component, enabling tailoring of the programme to meet patient needs (eg, returning to work, communicating with family members). Treatment planning will occur in collaboration with the treating clinician and the research team.^36^ CHAT seeks to provide participants with the tools to practice language themselves by using commercially available computerised aphasia programmes during treatment. Mobile technology, such as iPads and iPhones, is often used to maintain practice schedules. In addition, the CHAT programme links participants into community resources (eg, peer-led aphasia groups, stroke groups, interest groups and other professionals) to promote psychosocial well-being and participation.

Involvement of partners and family is integral to the programme. Support people, including family members, significant others and/or carers, are invited to participate in all programme elements, as able. This may include attendance at educational group sessions, participation in individual therapy, and technology training and support for computer-based therapy. Depending on the participant with aphasia’s therapy goals, support people may also be the direct recipient of intervention (eg, communication partner training).

##### Implementation strategy

The implementation strategy consists of six components based on behaviour change theories^31 37^ and factors influencing implementation of mICAPs/ICAPs,^11 29 30^ and will be tailored to each setting based on local barrier assessments. The components include the following:

**Executive, leadership and stakeholder support:** formal agreements to implement CHAT will be signed with participating health services and pre-implementation discussions will be undertaken with key stakeholders from each site to assess local implementation needs. Multidisciplinary team meetings will be conducted to educate about CHAT and promote the programme.**Specialist web-based educational training:** participating clinicians will complete a web-based educational training component following a site-specific delivery timetable. Training will include background evidence and rationale, the importance of improving aphasia practice, information on CHAT therapy components, treatment techniques and case examples. Video testimonials of people with lived experience of aphasia and the CHAT programme will be included.**Interactive workshop:** after completing the web-based training, clinical teams will attend in-person or online interactive workshops, with a focus on skills development, local barrier identification, problem-solving and team strategy identification.**Resource provision:** essential physical resources will be provided to support implementation, including therapy protocols, goal setting and therapy resources, and digital equipment (eg, iPads).**Ongoing implementation support:** the research team will provide ongoing implementation support to facilitate further barrier identification and collaborative problem solving. Members of the research team will also engage in joint clinical planning with participating clinical teams to monitor team progress and support selection of evidence-based therapies to address goals.**Site champions:** each health service will designate one to two site champions who will monitor and support implementation, identify ongoing barriers and act as intermediaries between the health service and the research team. Site champions will also attend an online monthly community of practice meeting that will focus on promoting peer-learning and sharing implementation experiences across services.

### Treatment of concomitant conditions alongside periods 1 and 3

Relevant concomitant care and interventions will continue alongside this study. Examples of other interventions that are permitted during the study include other areas of speech pathology practice (eg, swallowing, motor speech, voice, augmentative and alternative communication, fluency) as indicated, as well as other allied health and medical care/intervention. Participants will not be prohibited from accessing non-aphasia therapy-related services during their participation in this study.

#### Participants and recruitment

This study will involve four participant groups: (1) people with post-stroke aphasia, (2) their support person, (3) treating clinicians and students and (4) non-treating clinical stakeholders (eg, directors of speech pathology). Consent to participate in this study will be obtained from all participants following the provision of a written participant information and consent form (with an aphasia-friendly version for people with aphasia, see online supplemental file 1) and a face-to-face or online meeting to provide verbal explanation and further discuss participation in this research.

#### People with aphasia

People with post-stroke aphasia will be recruited from participating sites if they are aged 18 years or older at the time of consent, have had a documented stroke and present with aphasia as identified by a speech pathologist using either the Language Screening Test^38^ or the Comprehensive Aphasia Test (CAT^39^). People with aphasia who have significant comorbidities that would prevent participation in aphasia rehabilitation (as determined by the treating speech pathologist in consultation with the multidisciplinary team and research team) or who did not have functional English language skills prior to their stroke will be excluded. Due to the between-group design of this study, people with aphasia who have previously been enrolled in period 1 of the study (ie, usual care) will not be eligible to participate in period 3 of the study (ie, intervention). Eligible people with aphasia will be identified by site champions and speech pathologists within the service, in consultation with the treating medical team and the research team.

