### Study status

Recruitment for the usual care period of the study was undertaken from April 2023 to February 2025. The intervention transition occurred across health services from August 2024 to June 2025. The CHAT implementation phase commenced in April 2025 and is ongoing.

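### Patients can be deferred from usual care to CHAT, and neither the primary model nor the covariate rule deals with the selection this could cause

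*Protocol article*

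**What the plan says.** **Allocation.** The strengths and limitations list says that, because of the design's "allocation of people with aphasia based on time periods, various risks of bias are possible, including selection bias". Study periods fixes the order: usual care in years 1 and 2, CHAT in years 3 and 4.

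**Entry.** Under People with aphasia, participants must be "aged 18 years or older at the time of consent, have had a documented stroke and present with aphasia as identified by a speech pathologist" with one of two named tests. The comorbidity exclusion is a judgement, "as determined by the treating speech pathologist in consultation with the multidisciplinary team and research team". No limit on time since stroke is given for either period. The same section says that "people with aphasia who have previously been enrolled in period 1 of the study (ie, usual care) will not be eligible to participate in period" (the third, CHAT).

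**Who recruits.** "Eligible people with aphasia will be identified by site champions and speech pathologists within the service". Both the medical team and the researchers are to be consulted.

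**What services know.** Period 1: usual care says that services will be told to avoid, where possible, significant changes related to CHAT. Implementation strategy adds signed agreements to implement CHAT, site champions who support it, and this: "Multidisciplinary team meetings will be conducted to educate about CHAT and promote the programme".

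**Dates.** Study status reports: "Recruitment for the usual care period of the study was undertaken from April 2023 to February 2025". Transition ran across services from August 2024 to June 2025, and CHAT began in April 2025.

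**Analysis.** Data analyses, Implementation effectiveness, adjusts the primary median regression for clustering of patients by service and gives protection against residual confounding as the reason. Data analyses, Clinical effectiveness, adjusts the linear mixed models for potential confounders, including linear trends, and considers baseline characteristics as covariates where the groups differ significantly.

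**The concern.** The exclusion rule keeps the two groups independent and is not itself the fault. The difficulty is the incentive it creates when the order of periods is known. Enrolling a patient in usual care removes that patient's chance of CHAT within the study. Leaving the patient out appears to cost nothing, because period 1 care is the service's standard care in any case. A clinician who expects a patient to do well with an intensive programme therefore has a reason to wait, and no stated entry criterion makes waiting disqualifying.

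Deferred patients would tend to be later after stroke and perhaps chosen for motivation or capacity. Both could alter change on the CAT, the Communicative Effectiveness Index (CETI), the communication confidence scale and the stroke and aphasia quality of life scale. Both could also affect the more-than-30-hours indicator in the primary composite. The same patients would be missing from usual care. Any resulting difference would be read as an effect of CHAT.

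**Working it through.** **1. The plan's own figure.** The sample size for CETI is not in dispute. Inputs from Sample size: effect 9.08, random intercept SD 14.82, residual SD 8.17, two-sided alpha 0.05, power 80%.
- SD of one observation = √(14.82² + 8.17²) = 16.92.
- The two-sample formula gives 55 per group, with 80.3% power.
- 55 / 0.80 = 68.75, so 69 per group and 138 in total, as stated.

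**2. The period when deferral is most plausible.** Inputs from Study status, counting months inclusively.
- Usual-care recruitment, April 2023 to February 2025: 9 + 12 + 2 = 23 months.
- Overlap with transition, August 2024 to February 2025: 5 + 2 = 7 months.
- 7 / 23 = 30%.

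These are the earliest transition date and the latest usual-care date across services, so 7 months is the maximum overlap. At a given site it could be zero, because site dates are not given.

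**3. Does the primary model deal with deferral?** An adjustment for service handles differences between services and the correlation of patients within them. Deferral moves patients from one period to the other inside the same service. That contrast is exactly the one the model estimates, so the stated adjustment leaves it in place. The sentence giving protection against residual confounding as the purpose of the clustering adjustment claims more than the adjustment can do.

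**4. Does the significance rule catch it?** Assume a two-sided 5% test (the level is not stated) and 69 per group.
- Standard error of a standardised baseline difference = √(2/69) = 0.170 SD.
- Smallest significant difference = 1.96 × 0.170 = 0.33 SD.

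Suppose, as an assumption, that 10–30% of the CHAT group are deferred patients who differ by 0.5–1.0 SD on a prognostic characteristic. The imbalance from the CHAT side is then 0.1 × 0.5 = 0.05 SD to 0.3 × 1.0 = 0.30 SD, all below 0.33 SD. At 0.30 SD the chance of a significant test is about Φ(0.30/0.170 − 1.96) = Φ(−0.20), or 42%. If the same share were also lost from usual care, the range doubles to 0.10–0.60 SD and only its upper part would usually be caught.

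**5. What a shift in CETI could look like.** The shift equals the share deferred times their difference in expected change. Both inputs are assumed.
- 0.1 × 3 = 0.3 points, or 3% of 9.08.
- 0.2 × 5 = 1.0 point, or 11%.
- 0.3 × 8 = 2.4 points, or 26%.

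The sign is open: later time since stroke and greater motivation may pull in opposite directions.

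**The case against.** The strongest reply is that this is a disclosed limitation of a justified design. The article says that "various risks of bias are possible, including selection bias", ties this to allocation by period, and gives the funding model and equitable site participation as reasons. Recruiters act in consultation with the medical and research teams. The clinical models have planned covariate and trend adjustment. Most of the five primary indicators record what the service delivers, so patient selection has limited scope to move them. Screening logs and enrolment rules may be in the full protocol, which is not shown.

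Much of this stands, and it rules out several stronger readings that a reader might infer:
- *That the groups do differ by selection.* No baseline data and no deferred patient are shown. The document supports a risk only.
- *That recruiters knew the switch date.* They knew the order of periods; knowledge of the date is an inference. The promotional meetings are not shown to have taken place while usual care was recruiting.
- *That only CHAT could draw on a backlog.* The entry criteria are the same in both periods, so usual care could also enrol patients known to the service before April 2023.
- *That about 21 of 69 usual-care patients (69 × 7/23) are affected.* Patients recruited in the overlap months were enrolled in usual care, so they were not held back. The count does not measure deferral.
- *That a particular loss of power follows.* It would rest on an assumed shift and on power of exactly 80%, whereas the article says at least 80%.

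The reply does not answer the narrower gap. The general disclosure does not mention the incentive, the primary model has no stated case-mix adjustment, and the significance rule can pass over a relevant imbalance.

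**Conclusion.** The point holds as a risk that the stated analysis does not adequately address. Allocation by period, recruiters who know the sequence, and a bar on usual-care participants without any rule on patients passed over together make deferral possible. Adjustment for service in the primary model cannot correct it, and covariates chosen by baseline significance in the clinical models may miss it.

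The size and direction cannot be derived from the document. The only figure it supports is a calendar one: at most 7 of 23 recruitment months overlapped transition at some service. The CETI range of 0.3–2.4 points and the 0.05–0.30 SD imbalance are illustrations under stated assumptions, and neither describes the primary outcome. The conclusion also assumes that the full protocol contains no consecutive-enrolment rule or similar safeguard; if it does, the concern shrinks accordingly. The change is worth making because CHAT recruitment is ongoing and the analysis can still be fixed in advance.

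**What to change.** 1. Extract the dates of stroke onset and of first referral to the participating service for every participant in both groups.
2. Pre-specify time since stroke and baseline CAT severity as covariates in the primary median regression and in the four clinical models, whether or not they differ significantly at baseline. Reword the sentence on clustering so that it no longer claims to protect against confounding.
3. Add a symmetric sensitivity analysis restricted to patients first referred within the window of their own period at their site. It excludes CHAT participants known to the service before that site closed usual-care recruitment, and usual-care participants known before that site opened recruitment. Excluding only CHAT patients would compare new referrals with an unrestricted usual-care group.
4. Report the number excluded by group and site. State in advance what change in the estimate counts as material, and describe the result as sensitive to selection if that change is seen.

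The cost is two dates per participant and some analysis-plan wording, with a smaller sample and wider intervals in the sensitivity analysis. The restriction will also remove some patients who were never deferred, such as those who were missed or declined. It cannot restore patients missing from the usual-care group, so it tests robustness and does not remove the bias. No patient's access to CHAT changes.
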